#### Training of the intervention providers

Two intervention providers will receive the training. They both have postgraduate degrees in health sciences and they will take part in six two-hour sessions to develop the skills needed for autonomy-supportive counselling. The training sessions will be supported by printed material and include a group discussion section and a practice session with feedback. The topics of the six sessions were: a) The self-determination approach in behavior change interventions, b) Motivational interviewing strategies, c) Planning autonomy-supportive sessions tailored to the individual, d) Using autonomy-supportive communication/language, e) Applying the behavior change techniques in an autonomy-supportive way, and f) Profiling practice in hypothetical case studies.

#### Control group (health information group)

Participants allocated to the control group will receive printed general health information material of the kind used in usual health care services for older people. The envelope with the printed material (brochures, booklets etc.) will be mailed by post to the control group participants during months 1, 3, 6, and 9. The material is divided into four themes. The first theme is “Exercise”, the second “Nutrition”, the third “Cardiovascular diseases”, and the last “Type II diabetes”. We do not expect the control group to exhibit change in the primary outcome. After completing the post-intervention assessment, the participants of the control group will receive the same information booklet and hence the opportunity to be exposed to the same information as those in the intervention group.

#### AGNES intervention adherence plan

Several strategies for enhancing adherence are integrated into the study plan. For example, frequent contacts (e.g., follow up support, newsletters and health information mails) to decrease attrition and maximize completeness of the data collection; tailoring (e.g., via profiling, readability of printed materials) to increase acceptance and logistical support (e.g., convenient schedule appointments) to limit participant burden. Additionally, an adherence monitoring mechanism will be used to ensure fidelity to the intervention. Research group meetings take place twice per month to monitor the progress of the intervention and to ensure that the protocol plan will be followed. During the first ten face-to-face and five additional randomly selected sessions during the intervention year, the second trained counsellor, using a protocol checklist, will observe the study counsellor in order to give feedback and ensure that the counselling protocol is applied as planned. Moreover, the study counsellor will complete a one-page self-assessment checklist and will make notes after each face-to-face and phone call counselling session. Notes will also be used to feed future follow-up counselling phone calls. Participants who wish to discontinue participation in the study will be asked if they want to remain for the assessments only.

### Outcomes and measures

Table 2 lists all the measures of the study along with references, the data collection methods and time points.

**Table 2 Tab2:** Measures, data collection time points, methods and references in the AGNES intervention

Assessment / method / scale	Pre-	Mid-	Post-	References
Main outcome				
Active Aging (68 items UJACAS Scale)	HI	HI	HI	[4]
Secondary outcomes				
Psychological well-being (42-item Scale of psychological well-being)	HI	–	HI	[49]
Depressive symptoms (CES-D questionnaire; 20 items)	HI	–	HI	[50]
Quality of life (13-item OPQOL-brief questionnaire)	HI	–	HI	[52]
Personal goals (single item)	PhI	HI	HI	[62]
Life-space mobility (15-item LSA questionnaire)	HI	–	HI	[35]
Walking difficulty	HI	–	HI	[54]
Sense of autonomy outdoor mobility (five-item subscale of IPA)	HI	–	HI	[56]
One-week physical activity surveillance (with tri-axial accelerometers)	HI	–	HI	[58]
Self-reported habitual physical activity (eight-item YAPS)	HI	–	HI	[59]
Theory-based explanatory measures				
Perceived autonomy support (five items)	PhI	HI	HI	[63]
Autonomous-controlled motivation (eight items)	PhI	HI	HI	[64]
Attitude towards active aging (three items); Subjective norms of active aging (single item); Perceived behavioral control over active aging (single item); Intention for active aging (single item)	PhI	HI	HI	[65]
Descriptive measures				
Education (single item) & Perceived financial situation (single item)	HI	–	–	[66]
Physical health	HI	–	–	[67]
Lower extremity physical performance (SPPB)	HI	–	–	[69]
Maximal isometric handgrip strength (hand-held dynamometer)	HI	–	–	[71]
Cognitive functioning (19-item MMSE)	HI	–	–	[41]
Changes in life situation (five items)	PhI	HI	HI	–
Habitation (single item)	HI	–	–	–
Self-rated health (single item)	HI	–	–	[72]
Perceived age (single item)	HI	–	–	[73]
Perceived active aging (single item)	HI	–	–	[4]
Motivation for active aging (single item)	HI	–	–	[4]
Feeling of loneliness (single item)	PQ	–	–	[74]
Social contacts (three items)	PQ	–	–	[67]
Current hobbies (single item)	HI	HI	HI	–
Assessment debriefing (one item)	HI, PhI	HI	HI	–
Intervention debriefing (one item)	–	–	HI	–

For each assessment, according to the time point (pre, mid and post), the method of data collection is indicated as Home Interview (HI), Postal Questionnaire (PQ) or Phone Interview (PhI)

#### Main and secondary outcomes

##### Active aging

The main outcome measure is active aging. Active aging is assessed using the University of Jyväskylä Active Aging Scale (UJACAS) at all time points [4]. The UJACAS consists of 17 items: practicing memory, using a computer, advancing matters in one’s own life, exercising, enjoying the outdoors, taking care of one’s appearance, crafting or DIY, making the home cozy and pleasant, helping others, maintaining friendships, getting to know new people, balancing personal finances, making one’s days interesting, practicing artistic hobbies, participating in events, advancing societal/communal matters, and doing things according to one’s world view. For each item, participants are asked to rate (scale from 0 to 4) the strength of their striving to accomplish the activity, their ability and opportunity to perform the activity and their amount or frequency of doing the activity during the 4 weeks immediately prior to the measurement. Subscores (range 0–68) for the four dimensions of striving, ability, opportunities and activity are then calculated, with higher scores reflecting higher striving, better ability or opportunities, and higher activity. Similarly, a higher composite score (range 0–272) indicates a higher level of active aging. The scale has shown good psychometric properties and test-retest reliability [4].

##### Well-being

*Psychological well-being*

Is assessed using the 42-item version of the Scales of Psychological Well-Being at pre- and post-trial [49]. The 42 items divide into six components, each with seven items. The components are: (a) autonomy (e.g., “My decisions are not usually influenced by what everyone else is doing”), (b) environmental mastery (e.g., “In general, I feel I am in charge of the situation in which I live”), (c) personal growth (e.g., “For me, life has been a continuous process of learning, changing, and growth”), (d) positive relations with others (e.g., “Maintaining close relationships has been difficult and frustrating for me”; reverse scored), (e) purpose in life (e.g., “I have a sense of direction and purpose in life”), and (f) self-acceptance (e.g., “When I look at the story of my life, I am pleased with how things have turned out”). The participant rates the fit of each item on a six-point scale ranging from one (strongly disagree) to six (strongly agree). A total score for the whole scale is computed by summing the scores for the 42 items (range 42–252). Further, a sum score (range 7–42) is calculated for each of the seven components. Higher scores indicate higher psychological well-being.

*Depression*

The 20-item Centre for Epidemiologic Studies Depression Scale (CES-D) [50], is used to assess depressive symptoms at pre- and post-trial. The participant rates the frequency of twenty depressive symptoms during the previous week. The score for each item ranges between zero (rarely or none of the time) and three (most or all of the time). The total score ranges from 0 to 60, with higher scores indicating more depressive symptoms. The reliability and validity of the CES-D scale has been satisfactory [51].

##### Quality of life

Quality of life is assessed pre- and post-trial with a short version of the Quality of Life Questionnaire for Older People (OPQOL-brief). The scale includes 13 items related to life overall, health, participation, social relationships and financial situation. Answers are given on a scale from one (strongly disagree) to five (strongly agree). The sum score ranges from 13 to 65, with higher scores indicating higher quality of life. The scale’s reliability and validity, as a measure of overall quality of life, are satisfactory [52].

*Life-Space Mobility*

Life-space mobility reflects actual mobility performance in daily life and is assessed with the University of Alabama at Birmingham Study of Aging Life-Space Assessment (LSA) at pre- and post-trial [35]. The LSA comprises 15 items and assesses mobility through the different life-space levels (bedroom, other rooms, outside home, neighborhood, town, beyond town), frequency of movement, and need for assistance during the 4 weeks preceding the assessment. The composite score ranges from 0 to 120, higher scores indicating greater life-space mobility. The scale has good test-retest reliability [53].

*Walking difficulty*

Self-reported walking limitation is assessed pre- and post-trial as perceived difficulty in walking 500 m and 2 km [54, 55]. The response range is from one (able to manage without difficulty) to five (unable to manage even with help).

*Autonomy in outdoor mobility*

Perceived sense of autonomy in out-of-home activities, that is, the feeling of having control over the decision to go out whenever, wherever, and however one wants, is assessed pre- and post-trial with the ‘autonomy outdoors’ subscale of the Impact on Participation and Autonomy questionnaire (IPA), which has been validated [56, 57]. Participants rate their perceived opportunities for visiting relatives and friends, making trips and traveling, spending leisure time, meeting other people, and living life the way they want. The sum score ranges from 0 to 20, with higher scores indicating more restrictions on participation.

*Physical activity surveillance*

Willing participants wear a tri-axial accelerometer (13-bit ±16 g, UKK RM42, UKK Terveyspalvelut Oy, Tampere, Finland) continuously for 7 days following the home interview at pre- and post-trial. At post-trial, only participants who have worn the accelerometer at baseline are invited to participate. When wearing the accelerometer, participants keep a short written diary on their daily activities. The accelerometer is set to 100 samples per second. The accelerometer is attached to the anterior aspect of the mid-thigh of the dominant leg and covered with a waterproof self-adhesive film. Movement and non-movement behaviors are analyzed as the number of minutes spent at a particular activity intensity level (e.g. sedentary, light, moderate, and vigorous) [58].

*Self-reported habitual physical activity*

Self-reported habitual physical activity is assessed pre- and post-trial using the Yale Physical Activity Survey for older adults (YAPS; [59]) at the pre- and post-trial home interview. The YAPS questionnaire includes a physical activity dimension sum index, which is the sum of five weighted sub-indices (vigorous physical activity, leisure walking, moving around, standing and sitting) [59]. The total score ranges from 0 to 137, higher scores indicating higher physical activity. The reliability of the survey has been found to be fair [60].

#### Personal goals

Personal goals are asked using an open-ended question based on the Personal Project Analysis [61], but formulated for the purpose of studying older people’s goals [62]. Following a brief introduction on what is meant by personal goals, the participants can report all the goals they have. The total number of goals will be calculated for each participant. Moreover, the goals will be categorized into 25 goals categories and further into seven thematic goal dimensions based on their content [62].

### Theory-based explanatory measures

Additional explanatory data will be collected at baseline, mid- and post-trial, from both groups.

#### Perceived autonomy support

A modified short version of the Health Care Climate Questionnaire [63] is used to assess participants’ perceptions of the degree to which they experience their social environment as autonomy-supportive versus controlling with respect to active aging. Adjustments have been made regarding the context (social support, in general provided by people) and behavior assessed (active aging). The scale consists of five items (e.g.: “I feel that other people around me have provided me with choices and options to live an active life.”) and responses are given on a Likert-type scale ranging from: “1 = strongly disagree” to “7 = strongly agree”. An individual’s score on this scale is the average of his or her responses on the five items.

#### Autonomous-controlled motivation

The Self-Regulation Questionnaire [64] adapted to meet the needs of the intervention, is used to assess individual differences in the types of motivational regulation for being more active. The questionnaire consists of two sub-scales: autonomous motivation (4 items: e.g., “Because I enjoy being an active person”) and controlled motivation (4 items: e.g., “I would feel like a failure if I do not live an active life”). Answers are given on a Likert-type scale ranging from: 1 = “strongly disagree” to 7 = “strongly agree”. The participant’s score for each subscale is the mean score for the 4 items.

The constructs pertaining to the theory of planned behavior have been developed following the recommendations given in the manual for health services researchers [65] for the needs of the present study. *Attitude* towards being more active is assessed with 3 items scored on 7-point semantic differential scales ranging from 1 to 7 (“Aiming to live a more active life during the next six months means to me … pleasant - unpleasant, difficult - easy, useful - useless”). *Subjective norms of active aging* are assessed with one item: “I feel that the people who are important to me would want/expect me to live a more active life for the next six months”. Responses are given on a 7-point scale ranging from 1 = “strongly disagree” to 7 = “strongly agree”. *Perceived behavioral control over active aging* is assessed with one item: “I am confident that I can live a more active life for the next 6 months”. Responses are given on a 7-point scale ranging from 1 = “strongly disagree” to 7 = “strongly agree”. *Intention for active aging* is assessed using one item: “I intend to live a more active life for the next 6 months”. Responses are given on a 7-point scale ranging from: 1 = “strongly disagree” to 7 = “strongly agree”.

### Descriptive measures

#### Additional baseline measures

*Age* and *sex* are drawn from the population register. At baseline, *education* is assessed by number of completed years of education [66]. *Perceived financial situation* is assessed on a five-point scale ranging from one (very good) to five (very poor). *Physical health* is assessed based on self-reported physician-diagnosed diseases. A co-morbidity index similar to one previously used [67] is calculated from a checklist of diseases prompted by 10 categories of chronic diseases and an open-ended question about any other physician-diagnosed chronic conditions. *Lower-extremity physical performance* is assessed by the Short Physical Performance Battery (SPPB) [68–70]. The battery comprises tests on standing balance, walking speed over a 3-m distance, and the ability to rise from a chair. Established cut-off points are used to score each task from zero to four points [69, 70], higher scores indicating better performance. Participants unable to perform a test are assigned the score zero. A sum score is calculated (range 0–12) when at least two tests are completed. *Maximal isometric handgrip strength* is measured on the dominant side with a hand-held adjustable dynamometer (Jamar Plus digital hand dynamometer, Patterson Medical, 6 Cedarburg, WI, USA) and expressed in kg [71]. *Cognitive functioning.* Cognitive functioning is assessed with the Mini-Mental State Examination (MMSE) [41]. The MMSE contains 19 items and the score ranges from 0 to 30. *Changes in life situation.* Major changes in life situation are assessed with five questions on changes during the last 6 months in health status, mobility or functional ability, family situation or other social relationships, hobbies, and other major changes. Answer options are “No changes”, “Yes, positive changes”, “Yes, negative changes” and “Yes, both positive and negative changes”. Those reporting changes are then asked follow-up questions to gain specific information about the changes. Finally, participants are asked what change was most significant for them and what its impact was on their life.

#### Profiling measures

The following baseline measures will be used as additional information to individualize counselling: *Habitation* is categorized into living alone, with a spouse, with children or grandchildren, with siblings, relatives, or other people. *Self-rated health* is asked with the question: “How would you assess the current state of your health in general”? Answers are given on a five-point rating scale from one (very good) to five (very poor) [72]. *Perceived age*, i.e., how people experience their own aging on the personal level, is assessed with the question: “How old do you feel you are?” [73]. *Perceived active aging* is assessed by asking participants to evaluate how active their life is on a scale from 0 (not at all active) to 10 (very active) [4]. *Motivation for active aging* is assessed by asking participants how strongly they agree (1) or disagree (5) with the claim “I have special interests in my life” [4]. *Feeling of loneliness* is assessed with the question: “How often do you feel lonely?” Answers are rated on a four-point scale ranging from very rarely/never to almost always [74]. *Social contacts* are assessed with questions regarding the frequency of contacts with children and other relatives, close friends, and other acquaintances [67]. The response options are daily, weekly, monthly, a few times a year, rarely or not at all, and not having any children or other relatives/friends/acquaintances. *Current hobbies.* An open-ended question, “What are your most important hobbies?” is used to probe participants’ main hobbies. In addition, the measures of personal goals, active aging, well-being, life space mobility and depressive symptoms were used for profiling.

#### Debriefing questions

All interviews will end with an open-ended question asking participants whether they want to share any thoughts and feelings about the interview. Later, after completing the study, participants will be given the opportunity to share any other thoughts and feelings regarding their experiences of participation in the study.

### Data analysis

All analyses will primarily be performed using intention-to-treat analysis and supplemented by per-protocol analysis for all planned outcomes [75]. Means, standard deviations and frequencies will be calculated for continuous variables. Distributions will be tested for normality. The effects of the intervention will be assessed using repeated measures ANOVA and linear mixed models. Generalized estimating equations (GEE) models will be used to analyze differences in changes in discrete variables over the three time points. The level of statistical significance will be set at *p* < 0.05 (two-sided). Full information maximum likelihood (FIML) estimation under the assumption of data missing at random (MAR) will be used to analyze incomplete data. Multiple imputation methods will be used to complete the dataset if necessary. Non-respondent analyses for those who declined to participate will be performed, based on the cohort baseline data. Subgroup analyses for sex, age, socioeconomic status, cognitive (MMSE) and mobility (SPPB) function will also be performed. In all future publications, data will be reported following the criteria recommended by the CONSORT guidelines.

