### Sequence generation and the allocation concealment mechanism

Stratified randomization for age and sex will be used with a 1:1 allocation to ensure a good balance of participant characteristics in each group. The randomization sequence will be created using Stata 15.0 statistical software (StataCorp, College Station, TX) by the study statistician, who immediately after generation of the random allocation sequence will seal them in envelopes.

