### Sample size and power calculations

A total of 168 participants are needed for a 90% probability to detect a treatment difference at a two-sided 0.05 significance level, if the true difference in the main outcome between the intervention and the control group is 10%. As some of the participants may be vulnerable and the intervention is long, 200 participants will be needed to allow for the potential attrition rate of 20% during this time. The power calculations are based on estimates from two earlier studies [37, 38].

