### Participants

#### Eligibility criteria

The AGNES intervention will recruit participants from the ongoing AGNES cohort study [39], which is an observational study of three age cohorts (75, 80, and 85 years) living independently in the municipality of Jyväskylä, Finland. Inclusion criteria for the RCT study will be age 75 or 80, a baseline score between 52.3 and 90.0 on the University of Alabama at Birmingham Life-Space Assessment (LSA; [35, 40]), and a score of 25 or higher on the cognitive function test (MMSE; [41]). Recruitment has started in October 2017 and will continue until the number of participants reaches 200.

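### The effect model leaves open how baseline and the randomisation strata enter; read as the usual group-by-time test, it is less precise than a baseline-adjusted model

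*Protocol article*

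**What the plan says.** The Data analysis section of the protocol article gives one sentence on the effect analysis of continuous outcomes: "The effects of the intervention will be assessed using repeated measures ANOVA and linear mixed models". It lists no fixed effects, no handling of the baseline value and no contrast for the primary test. GEE models of differences in change are described in a separate sentence, but for discrete variables only.

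On allocation, the section on sequence generation says: "Stratified randomization for age and sex will be used with a 1:1 allocation". In the Data analysis section, age and sex return only in the list of subgroup analyses.

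On the primary outcome: "Active aging is assessed using the University of Jyväskylä Active Aging Scale (UJACAS) at all time points". A baseline value and two follow-up values are therefore planned for each participant. Table 2 shows that every secondary outcome except personal goals is measured only before and after the trial.

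The sample size section says: "A total of 168 participants are needed for a 90% probability to detect a treatment difference at a two-sided 0.05 significance level". The effect to be detected is put at 10% of the primary outcome, without a scale. The section adds that "The power calculations are based on estimates from two earlier studies". No SD, reference mean or baseline-to-follow-up correlation is given. On attrition: "200 participants will be needed to allow for the potential attrition rate of 20% during this time".

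**The concern.** The two named model families are not interchangeable. In a repeated measures ANOVA the pre-trial score is one of the repeated responses, and the treatment effect is normally read from the group-by-time interaction. With two time points that interaction is algebraically a two-sample test on change scores. With three, the baseline-to-12-month part of it is again a difference in mean change.

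In a randomised trial the true baseline means are equal. A change-score analysis does not use that fact; a model with baseline as a covariate, or with a common baseline mean in both arms, does. At stake are wider intervals and lower power than the collected data allow, for the primary outcome and for the continuous secondary outcomes. Naming two families of different efficiency also leaves the primary estimate open to choice.

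The strata are a smaller matter of the same kind. Leaving age and sex out after stratifying on them does not bias the estimate, but it tends to make standard errors slightly too large.

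**Working it through.** **Inputs from the protocol article.** Two-sided α 0.05, power 90%, 168 evaluable (84 per arm at 1:1), 200 recruited, 20% attrition. Completers at that attrition: 200 × (1 − 0.20) = 160, or 80 per arm.

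**Inputs not given, so assumed.** The SD of UJACAS and ρ, its correlation between baseline and follow-up. ρ is shown over a range.

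**The plan's own figure.** The 168 cannot be recomputed from stated inputs. Solving backwards, d = (1.960 + 1.282) × √(2/84) = 0.500. This fits an SD of about 20% of the mean if the 10% difference is relative to that mean. With d = 0.50 the normal formula gives 85 per arm, 170 in total, within 3% of 168. So d = 0.50 is a fair working value, but it is inferred, and so is the assumption that it refers to the follow-up SD.

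**Formulas.** With equal variances at baseline and follow-up, relative to the follow-up variance:

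- change score: 2(1−ρ)
- baseline-adjusted (ANCOVA or common baseline mean): 1−ρ² = (1−ρ)(1+ρ)
- ratio adjusted/change: (1+ρ)/2, which never exceeds 1

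The effective standardised difference is 0.50 divided by the square root of the variance factor. At ρ = 0.4 it is 0.50/√1.20 = 0.456 for change and 0.50/√0.84 = 0.546 for the adjusted analysis.

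**Power, two-sample t-test, 80 per arm:**

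| ρ | Variance, change | Variance, adjusted | Ratio adjusted/change | Power, change | Power, adjusted |
|---|---|---|---|---|---|
| 0.4 | 1.20 | 0.84 | 0.70 | 81.8% | 92.9% |
| 0.5 | 1.00 | 0.75 | 0.75 | 88.2% | 95.2% |
| 0.6 | 0.80 | 0.64 | 0.80 | 94.0% | 97.6% |
| 0.7 | 0.60 | 0.51 | 0.85 | 98.2% | 99.3% |

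**As sample size.** Total evaluable participants for 90% power, change against adjusted (normal approximation): 170 against 128 at ρ = 0.5, 102 against 86 at 0.7, and 68 against 62 at 0.8.

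**Strata.** If age and sex explain a share R² of the outcome variance, the variance is multiplied by 1−R². With assumed R² of 0.02, 0.05 and 0.10 at 84 per arm, power rises from 90.0% to 90.5%, 91.4% and 92.7%.

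**The case against.** The strongest objection is that the article is silent on covariates and does not say it will omit them. An article condenses a fuller plan, and covariate lists are commonly left to that plan. Linear mixed models are already named, and both remedies proposed here for UJACAS are linear mixed models. This stands in part. A reader might infer that the plan has chosen an unadjusted analysis, and the text does not support that. The phrase about differences in change does not supply it either, since it belongs to the discrete variables. What remains is that repeated measures ANOVA is named as an effect analysis, and its usual test is the less efficient one.

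Second, the size rests on unstated inputs. This stands. If the planning SD was an SD of change, a change-score analysis has its planned power by construction. Adjustment would then raise 90% at 84 per arm to 96.3% at ρ = 0.5, 94.0% at 0.7 and 92.7% at 0.8: a gain, but no loss against plan. Nor does the sample size section claim any adjustment, so one cannot say that planned precision is being discarded.

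Third, a reader might infer that life-space mobility suffers most, because entry requires "a baseline score between 52.3 and 90.0 on the University of Alabama at Birmingham Life-Space Assessment" and selection lowers its correlation with follow-up. This does not follow. The formulas above assume equal variances, and selection on the baseline breaks that. Under a linear model the slope b and the residual variance are unchanged by such selection. The change-score variance is (1−b)² × Var(baseline) + residual, against the residual alone for ANCOVA. With an unselected ρ of 0.5 and a standard normal baseline (assumed), the ratio of change to adjusted is (0.25 × 1 + 0.75)/0.75 = 1.33 without selection. With the baseline kept within ±1 SD, where its variance is 0.291, it is (0.25 × 0.291 + 0.75)/0.75 = 1.10. Selection shrinks the penalty.

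**Conclusion.** The point holds as a choice of method that should be improved, not as an error in what the plan states. One of the two named methods, used in the ordinary way, compares change scores and is never more efficient than a baseline-adjusted analysis. This is exact for outcomes measured only before and after the trial.

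The size depends on ρ, which is not given. With d = 0.50 on the follow-up SD and 80 per arm, the gain in power is about 11 points at ρ = 0.4, 7 at 0.5, 4 at 0.6 and 1 at 0.7. Where ρ is high, power hardly moves, but change-score intervals are still wider: at ρ = 0.7 by a factor of √(1/0.85) = 1.08. Adding age and sex brings a small gain and corrects slightly conservative standard errors; no bias is at issue.

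**What to change.** In the Data analysis section:

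1. Remove repeated measures ANOVA as an effect analysis.
2. State the primary model: a linear mixed model for 6- and 12-month UJACAS with arm × time, baseline UJACAS × time, age cohort and sex. A constrained longitudinal model with a common baseline mean in both arms, with the same strata terms, is an equally good alternative.
3. For continuous secondary outcomes measured only before and after the trial, use ANCOVA on the post-trial value with its own baseline value, age cohort and sex.

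The cost is a few sentences. UJACAS and the secondary outcomes are already measured before the trial (Table 2), and age and sex come from the population register. No extra data or participants are needed. If an analysis plan already specifies such models, it is enough to bring the protocol wording into line with it.
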